# Evaluating and Optimizing Just-in-Time Adaptive Interventions in a Digital Mental Health Intervention (Wysa for Chronic Pain) for Middle-Aged and Older Adults With Chronic Pain: Protocol for a Series of Randomized Trials

**DOI:** 10.2196/77532

**Published:** 2025-09-17

**Keywords:** anxiety, chronic pain, depression, digital mental health intervention, engagement, human-centered design, just-in-time adaptive intervention, microrandomized trial, middle-aged adults, older adults

## Abstract

**Background:**

On a population level, digital mental health interventions effectively reduce depression and anxiety symptoms. However, middle-aged and older adults with chronic pain and coexisting depression or anxiety have not been adequately represented in digital mental health studies.

**Objective:**

The goal of this study is to refine an existing mobile, digital mental health intervention (Wysa for Chronic Pain) that addresses symptoms of depression, anxiety, and coexisting chronic pain for the unique challenges and technology use patterns of middle-aged and older adults.

**Methods:**

Using a mixed methods, human-centered design approach and a series of randomized trials, we will test and iteratively refine just-in-time adaptive interventions (JITAIs) that are designed to increase engagement with a digital mental health intervention. Participants will be aged 45 years or older, endorse at least moderately severe depression or anxiety symptoms (Patient Health Questionnaire-9 or Generalized Anxiety Disorder-7 score ≥10), and have coexisting chronic pain (ie, pain on most days or every day in the past 3 months), and live in the United States. In this open, web-based trial, participants will all receive Wysa for Chronic Pain (by Wysa), which uses a behavioral activation framework and encourages users to work toward pain acceptance. The fully automated intervention also includes cognitive behavioral therapy, mindfulness, and sleep tools, among others. In each trial, participants will be randomized during a maximum 12-week study period to receive versus not receive novel JITAIs that are intended to reduce navigation burden and improve usability (and subsequent engagement and clinical effectiveness). The JITAIs are being designed with iterative user feedback, guided by the Discover, Design/Build, and Test framework and the Behavioral Intervention Technology model. The proximal outcome for each JITAI is related to engagement with Wysa for Chronic Pain after JITAI delivery (compared to when no JITAI is delivered). The primary distal clinical outcome is the Patient Health Questionnaire Anxiety and Depression Scale. Based on statistical analysis that is triangulated with qualitative feedback from a subsample of trial participants, the JITAIs will be iteratively refined and retested in subsequent microrandomized trials until retesting of refined adaptations no longer yields meaningful improvement in immediate engagement or a maximum of 5 total trials have been completed.

**Results:**

Institutional review board approval was obtained on April 11, 2025. The first participant was enrolled on June 2, 2025, and recruitment is expected to conclude in 2026.

**Conclusions:**

Completion of this project will result in iteratively refined JITAIs that are designed to improve usability and engagement with a digital mental health intervention by middle-aged and older adults with depression or anxiety and coexisting chronic pain.

**Trial Registration:**

ClinicalTrials.gov NCT06978166; https://clinicaltrials.gov/study/NCT06978166

**International Registered Report Identifier (IRRID):**

PRR1-10.2196/77532

## Introduction

### Background

The prevalence of chronic pain increases with age, and among the 26% of middle-aged and 31% of older adult Americans with chronic pain, up to half experience depression or anxiety [1-4]. At a population level, digital mental health interventions effectively address many access barriers to mental health care and reduce depression and anxiety symptoms [5-10]. However, middle-aged and older adults with coexisting chronic pain have not been adequately represented in digital mental health intervention studies. This gap is important to address for these populations for multiple reasons: (1) chronic pain reduces the effectiveness of stand-alone mental health treatment unless a person’s pain is simultaneously addressed [11,12]; (2) physical and mental health–related disability in these older age groups has unique downstream effects, such as reductions in the workforce, impact on dependent children, and strain on caregiver availability [13-17]; and (3) use of technology in these age groups is widespread and growing, but these users have unique digital health needs and preferences [5-7,18-21]. Compared to younger users, middle-aged and older adults have unique needs for mental health interventions. For example, they prefer more access to real-time support that supplements automated instructions; they have a greater interest in interventions that address multimorbidity; they prefer different screen layouts due to age-related changes in visual acuity, eye tracking patterns, and dexterity; and they may benefit from more “push” notifications because they check their phones less frequently, and some have age-related cognitive deficits that reduce their ability to independently navigate through apps [18,22-26].

### Wysa for Chronic Pain

Wysa is an established, evidence-based mobile app with over 6.5 million users, and it has the potential to meet the digital mental health care needs of middle-aged and older adults [27,28]. It is available directly to consumers through free and paid subscriptions, and some versions of the platform are covered by select employers and insurers. It delivers evidence-based mental health therapeutic techniques like cognitive behavioral therapy through an artificial intelligence–based chatbot [29,30]. Wysa for Chronic Pain is a specific version of the platform for people with mental health symptoms and coexisting chronic pain [31]. Preliminary studies have demonstrated encouraging signals of effectiveness for Wysa for Chronic Pain among adults across the age spectrum [32-34]. However, middle-aged and older adults specifically identified barriers to engagement related to navigation difficulty within Wysa for Chronic Pain [34].

### Just-in-Time Adaptive Interventions

Just-in-time adaptive interventions (JITAIs) are a unique approach that uses prespecified triggers and leverages user data to deliver a digital intervention, specifically when a person is most in need and receptive to the intervention [35-37]. For instance, a user who is trying to increase physical activity may receive a daily smartphone prompt to encourage physical activity, but only if passive sensors from the smartphone detect that the user is not already active, is not driving or riding in a vehicle, and has not yet met their step goal for the day [38]. Because JITAIs can be pushed to a user when they are most relevant (rather than requiring user-led navigation), JITAIs are particularly appropriate for people with difficulty navigating digital tools. In academic studies, JITAIs have shown promise in driving engagement and improving effectiveness to increase emotional regulation, exercise, and other healthy behaviors; however, the use of JITAIs in commercial digital mental health interventions is relatively novel [39-42].

### Goal of This Study

We are conducting a large-scale, 3-phase project using human-centered design and the Discover, Design/Build, and Test (DDBT) framework to optimize an existing digital mental health intervention (Wysa for Chronic Pain) for middle-aged and older adults with depression or anxiety and coexisting chronic pain [43]. In the first project phase, we conducted semistructured interviews and usability testing among this target user population. During that process, novel JITAIs for Wysa for Chronic Pain were developed using the Behavioral Intervention Technology (BIT) model [36,44], which links established behavior change strategies with technology-related design and implementation factors—for example, timing, medium (text, audio, or video), and complexity of intervention delivery—that affect engagement and subsequent effectiveness of a digital health intervention [44,45].

This study protocol outlines the second project phase. In a series of traditional and microrandomized trials (MRTs) that are interspersed with qualitative feedback from a subgroup of trial participants, the goal of this study is to test and optimize the effectiveness of the novel JITAIs to increase engagement among middle-aged and older adults with Wysa for Chronic Pain. The central hypothesis is that incorporating these JITAIs will increase engagement with Wysa for Chronic Pain by improving usability and, subsequently, will improve depression and anxiety symptoms in this population. After completion of this phase, the third project phase will be a pragmatic, hybrid type 1 effectiveness-implementation trial during which the final JITAIs will be fully integrated into the Wysa for Chronic Pain user experience.

## Methods

### Study Design and Setting

In this remote, single-site, mixed methods study, we will conduct a series of randomized trials interspersed with semistructured interviews (Figure 1). The first trial will be a traditional 4-week, 2-arm randomized controlled trial in which participants receive “Wysa for Chronic Pain with JITAIs” or “Wysa for Chronic Pain without JITAIs.” The primary purpose of this first trial is to obtain preliminary information regarding the frequency that (1) the prespecified criteria (ie, decision rules) are met for each JITAI and (2) participants engage with each JITAI. These quantitative data, coupled with qualitative data from semistructured interviews with a subgroup of trial participants, will guide the final design (and particularly the initial randomization probabilities) of a subsequent 12-week MRT. MRTs were developed as a novel study design by Susan Murphy and colleagues [46] to rigorously study JITAIs. In an MRT, each participant is repeatedly randomized multiple times during the course of the trial. For example, randomization can be related to (1) receiving one versus another JITAI (or none at all) when fixed prespecified criteria are met or (2) variations in the prespecified criteria or delivery of a JITAI (eg, timing for the decision rule, timing of JITAI delivery, JITAI language, etc). In this way, both between-participant and within-participant comparisons can be made, which increases the efficiency of the trial. Furthermore, time-varying effects of a JITAI can be studied with an MRT, for instance, to evaluate a JITAI’s impact on engagement during the first day of app use (when engagement is typically high) compared to the tenth week of app use (when engagement is typically lower) [46].

**Figure 1 figure1:**
[figure not shown]
Study design. JITAI: just-in-time adaptive intervention; MRT: microrandomized trial; RCT: randomized controlled trial.

We anticipate performing 2-4 MRTs as part of this study, depending on opportunities that we identify for continued JITAI refinement based on our quantitative and qualitative findings after each trial, within the limitations of time and budget constraints. Each MRT will include 2 arms (Figure 2). Participants in the “Wysa for Chronic Pain with JITAIs” intervention arm will be randomized every time they meet prespecified criteria (ie, decision rules) for the JITAIs under investigation, whereas participants in the “Wysa for Chronic Pain without JITAIs” control arm will never receive JITAIs, regardless of whether they meet the prespecified criteria. Inclusion of a control arm in each trial will facilitate accounting for time-varying factors (eg, refinements to the Wysa for Chronic Pain user experience that are unrelated to the JITAIs) and enable additional secondary analyses.

**Figure 2 figure2:**
[figure not shown]
Participant flowchart for each microrandomized trial (MRT). JITAI: just-in-time adaptive intervention.

### Participants

#### Eligibility Criteria

Eligibility criteria were selected to be pragmatic and reflect the broad target population for Wysa for Chronic Pain while also being mindful of which variables can reliably be collected in an entirely remote study (Textbox 1).

Eligibility criteria.
**Inclusion criteria**
Aged 45 years or olderAt least moderately severe depression or anxiety symptoms (Patient Health Questionnaire-9 or Generalized Anxiety Disorder-7 score ≥10) [47,48]Chronic pain (ie, pain on most days or every day in the past 3 months) [2]
**Exclusion criteria**
Frequent active suicidal ideation [49]No access to a mobile deviceNot living in the United States

#### Sample Size

Sample size calculations were performed at a 5% significance level to detect an effect in the primary study outcome between the 2 study arms. Because the primary outcome for each JITAI is related to engagement (which is automatically captured by the Wysa platform and does not require participant report), we assumed a 10% attrition rate (conservatively assessed as occurring at baseline but after downloading Wysa for Chronic Pain). In the initial 4-week pilot trial, we will enroll 29 participants into each of the 2 arms (58 participants total). This will provide 80% power to detect a large effect size (Cohen *d*=0.8).

Sample size determinations for the subsequent 12-week MRTs will be dependent on analysis after each preceding trial, but it is anticipated that control groups for analysis will be pooled by including the control groups from previous trials. For the first MRT, we preliminarily anticipate enrolling 75 participants into the “Wysa for Chronic Pain with JITAIs” intervention arm and 46 participants into the “Wysa for Chronic Pain without JITAIs” control arm (121 total participants recruited). In the intervention arm, clipped Thompson sampling will be used to make intervention assignments with the clipping rate set at 10%. This would provide 80% power to detect a moderate to large effect size (Cohen *d*=0.5). For the second MRT, we preliminarily anticipate enrolling 120 participants into the intervention arm and 55 participants into the control arm (175 total participants recruited). Clipped Thompson sampling will again be used in the intervention arm, with a 10% clipping rate. This would provide 80% power to detect a moderate to small effect size (Cohen *d*=0.4). Sample sizes for any additional MRTs will follow a similar calculation process.

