#### JITAIs Descriptions

Multiple JITAIs will be tested in the trials. Table 1 describes the JITAIs that will be tested in the first trial, but the final plan for each subsequent trial will be refined based on findings from the preceding trials and semistructured interviews. Each proposed JITAI in Table 1 involves the delivery of one or more push notifications to the participant. The notifications are intended to improve engagement in numerous ways, such as directing a user to a relevant therapeutic tool, adjusting the Wysa for Chronic Pain experience and frequency of scheduled notifications in order to meet the user’s demonstrated preferences and to reduce notification fatigue, and increasing the frequency of scheduled notifications when mental health symptoms have recently worsened.

**Table 1 table1:** Description of initial just-in-time adaptive interventions (JITAIs) to be tested in the microrandomized trials.

JITAI name	Purpose	Decision rule: tailoring variables and cut points	Decision rule: intervention^a^
Onboarding	Increase onboarding completion rates	If the user downloaded the app but did not complete onboarding within 24 hours of download	Then, send a notification that encourages the user to finish onboarding. The notification directs the user back to the onboarding screen. When possible, the notification is personalized based on information the user shared thus far during onboarding.
Short disengaged	Motivate a user to engage using messages or content that resonates with the user	If no app engagement for 24 hours	Then, send a personalized notification regarding a challenge the user endorsed at onboarding or during a previous conversation. The notification directly opens to a relevant tool.
Long disengaged	Respect that users’ preferred or needed frequency of engagement may fluctuate based on symptom severity and life events	If no app engagement for 7 days	Then, send an “FYI^b^ or opt back in”^c^ notification, and stop all notifications for 3 days. After 3 days, send a notification with a tool that was previously helpful or that has not been used yet but should be relevant based on challenges reported at onboarding. Then resume the previous notification schedule.

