AM check-ins only	Personalize push timing to users’ demonstrated preferences	If no engagement with PM check-ins but ≥1 engagement with AM check-ins within the last 7 days	Then, send an “FYI or opt back in” notification, stop daily “PM check-in” notifications, and move the “activity tracking and mood reflection” task to the AM check-ins.
PM check-ins only	Personalize push timing to users’ demonstrated preferences	If no engagement with AM check-ins but ≥1 engagement with PM check-ins within the last 7 days	Then, send an “FYI or opt back in” notification, stop daily “AM check-in” notifications, and move the “activity scheduling and planning” task to the PM check-ins.
Sporadic engagement only	Personalize push timing and content to users’ demonstrated preferences (eg, engagement only during pain or mood symptom flares)	If no engagement with AM or PM check-ins, but ≥1 user-led engagement within the last 7 days	Then, send an “FYI or opt back in” notification, and stop daily “AM check-in” and “PM check-in” notifications. Instead, each day, send a single personalized notification that directs the user to a tool that was previously helpful or that has not been used yet but should be relevant based on challenges the user reported at onboarding.
Mental health flare^d^	Offer increased support when most needed	If PHQ-4^e^ score worsens compared to the preceding PHQ-4 score, and the user’s current push notification frequency is less than twice daily	Then, send an “FYI or opt out” notification, and increase notification frequency back to twice daily (ie, AM and PM check-ins).

^a^For the “onboarding” and “mental health flare” JITAIs, the intervention will be delivered immediately after the decision rule cut points are met. For all other JITAIs, the intervention will be sent after a strategic delay. If the user’s previous 3 engagement events with the app are within the same 6-hour interval of the day, the initial notification of the intervention will be sent at the time of day equal to the average of the user’s last 3 engagement events (ie, when the user has historically been more likely to engage). Otherwise, the notification will be sent at the last time of day the user entered the app.

^b^FYI: for your information.

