### Statistical Methods

#### Primary Outcome

The main purpose of the initial 4-week pilot trial is to determine the initial randomization probability for each JITAI in the first MRT for the “Wysa for Chronic Pain with JITAIs” intervention arm (ie, to construct a robust informative prior, also called a warm start, for each JITAI). We will also perform between-group comparisons of the primary proximal outcome for each JITAI between the intervention versus control arm (ie, comparison of the primary engagement outcome during the target engagement time interval between participants in the intervention arm when they met prespecified criteria and received JITAIs vs participants in the control arm when they met the same prespecified criteria but did not receive JITAIs). In the subsequent MRTs, analysis of the primary proximal outcome for each JITAI will account for both between-group and within-participant comparisons because participants in the “Wysa for Chronic Pain with JITAIs” arm may have met the prespecified criteria for any given JITAI multiple times during the study period. A secondary analysis of each MRT will also be performed to again construct a prior (warm start) for the subsequent MRT, for instance, centered at the estimated optimal JITAI strategy.

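### The pilot's 80% power counts every participant left after attrition, but each JITAI's primary comparison includes only those who trigger that JITAI, at a rate not yet known

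*Protocol article*

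**What the plan says.** The Sample Size section of the protocol article describes one two-arm calculation per trial: "Sample size calculations were performed at a 5% significance level to detect an effect in the primary study outcome between the 2 study arms". The only reduction in numbers is for attrition: "we assumed a 10% attrition rate (conservatively assessed as occurring at baseline but after downloading Wysa for Chronic Pain". For the pilot, "we will enroll 29 participants into each of the 2 arms (58 participants total", followed by the unconditional statement "This will provide 80% power to detect a large effect size", with d=0.8.

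The article has no single primary study outcome. Table 2 gives each of the seven JITAIs its own primary proximal outcome, measured in a window after that JITAI's trigger. The Primary Outcome section then defines the pilot comparison as one between "participants in the intervention arm when they met prespecified criteria and received JITAIs vs participants in the control arm when they met the same" criteria without receiving the JITAI.

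The triggers in Table 1 are selective. Onboarding applies only to users who have not finished onboarding 24 hours after download. Long disengaged reads "If no app engagement for 7 days". Sporadic engagement only reads "If no engagement with AM or PM check-ins, but ≥1 user-led engagement within the last 7 days". Study Design and Setting lists the frequency with which these rules are met among the things the pilot is primarily meant to learn.

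For the MRTs, Sample Size gives 75 v 46 participants (d=0.5) and 120 v 55 (d=0.4), each at 80% power. It expects to pool controls from previous trials and calls the numbers preliminary.

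**The concern.** A participant who never meets a JITAI's decision rule has no outcome for that JITAI and cannot enter its comparison. The number that determines power is therefore the number who trigger, not the number enrolled less attrition. The article states 80% without any allowance for this, while saying elsewhere that trigger frequency is still to be learned.

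At stake is how a pilot result is read. A flat comparison for a JITAI that half of each arm triggered would rest on about 13 people per arm. Taken with the stated 80%, it could be read as fair evidence against a large effect when it is close to a coin toss. The pilot results also feed the starting probabilities and the refinement of the JITAIs for the first MRT.

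**Working it through.** **Inputs from the article (Sample Size):** 5% significance level; 10% attrition; pilot 29 per arm, d=0.8; MRT 1 75 v 46, d=0.5; MRT 2 120 v 55, d=0.4.

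**Assumptions:** two-sided test (sidedness is not stated); the same trigger share f in both arms; one outcome per person unless stated; d applied to every outcome, as the article does. The article gives no value for f, so a range is shown.

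**Formula.** Two-sample t-test with df = n1 + n2 − 2 and noncentrality δ = d × √(n1·n2/(n1+n2)), which is d × √(n/2) for equal arms. Power is the probability that a noncentral t exceeds the two-sided 5% critical value in absolute size.

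**Step 1: reproduce the pilot figure.** 29 × 0.9 = 26.1, so 26 per arm. δ = 0.8 × √13 = 2.88, critical t = 2.01, power 80.7%. The stated 80% is this test on everyone left after attrition.

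**Step 2: apply the protocol's own restriction.** Replace 26 by 26 × f.

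| Share triggering | n per arm | δ | Critical t | Power at d=0.8 | d detectable at 80% |
|---|---|---|---|---|---|
| 100% | 26.0 | 2.88 | 2.01 | 81% | 0.79 |
| 90% | 23.4 | 2.74 | 2.01 | 76% | 0.84 |
| 75% | 19.5 | 2.50 | 2.03 | 68% | 0.92 |
| 50% | 13.0 | 2.04 | 2.06 | 50% | 1.15 |
| 25% | 6.5 | 1.44 | 2.20 | 26% | 1.71 |

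Carrying 26.1 instead of 26 gives 1.14 and 1.70 in the last two rows. Power reaches a full 80% only when f is about 98%.

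**Step 3: repeated triggers in the pilot.** With m outcomes per person and within-person correlation ρ (both assumed), the effective number per arm is n·m/(1 + (m−1)ρ). At f=75% and m=2, this is 19.5 × 2/1.3 = 30.0 for ρ=0.3 and 19.5 × 2/1.5 = 26.0 for ρ=0.5, giving about 86% and 81%. At f=50% and m=2, it is 26/1.3 = 20.0 and 26/1.5 = 17.3, giving about 69% and 63%. Repeats can restore 80% for a frequent JITAI. Onboarding has m=1, so Step 2 applies to it unchanged.

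**Step 4: the MRT figures.** MRT 1 with pilot controls pooled: (46+29) × 0.9 = 67.5 v 75 × 0.9 = 67.5, power 82%. Unpooled, 67.5 v 41.4 gives 71%. MRT 2 with the controls of both MRTs: 120 × 0.9 = 108 v (46+55) × 0.9 = 90.9, power 80%. Adding the pilot controls (117) gives 85%; unpooled, 108 v 49.5 gives 64%. Both stated figures therefore need pooled controls and everyone left after attrition contributing an outcome.

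With one outcome per person, the pooled figures (67.5 v 67.5 and 108 v 90.9) become:

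| Share triggering | MRT 1, d=0.5 | MRT 2, d=0.4 |
|---|---|---|
| 90% | 78% | 76% |
| 75% | 70% | 68% |
| 50% | 53% | 50% |
| 25% | 29% | 28% |

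**Step 5: within-participant information in the MRTs.** For the within-person contrast alone, the variance is about (1−ρ)/(n(m−1)p(1−p)), where p is the delivery probability. In MRT 1 with n=67.5, m=5, ρ=0.3 and p=0.5 (the last three assumed), this is 0.7/67.5, so the standard error is 0.102. Then 0.5/0.102 = 4.9, and power exceeds 99%. With m=1 there is no within-person contrast.

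**The case against.** The strongest reply is that the pilot is mainly there to measure trigger frequency and build starting priors, that refinement is triangulated with interviews, and that no rule in the article drops a JITAI on a null test. That is fair and limits the harm. It does not make the stated power correct.

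Three stronger readings are tempting, and the article does not support them.

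- **That the MRT power figures fail.** The one-outcome figures in Step 4 are not the planned analysis. The Primary Outcome section says the MRT analysis uses both between-group and within-participant comparisons, and Step 5 shows how much repeated triggers can add. The MRT sizes are labelled preliminary and dependent on earlier trials, and a condensed article may leave their detailed inputs to the full protocol.
- **That 10% clipping dilutes the effect.** The pilot delivers the JITAI at every trigger, so its figure is untouched. In the MRTs, a strict arm comparison at 90% delivery would give 74% and 71% (d of 0.45 and 0.36). Analysed by what was delivered at one decision point, the contrasts are 60.75 v 74.25 and 97.2 v 101.7, and power stays at 82% and 80%. The article does not describe a comparison by arm alone. Lower delivery would cost power on a single decision point (about 70% in both MRTs at 50% delivery).
- **That no more than a quarter of participants can trigger each 7-day rule.** Long disengaged, AM only, PM only and Sporadic exclude one another on a single 7-day look-back. That does not cap the share who ever trigger each one over 4 or 12 weeks, and the shares need not be equal. The 25% row is an illustration, not a bound.

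**Conclusion.** The pilot statement is wrong as written. Its 80% is conditional on nearly all 26 participants per arm triggering the JITAI in question, yet it is stated without that condition, against a comparison that the same article restricts to those who trigger. If half trigger, with one outcome each, power at d=0.8 is 50% and the effect detectable at 80% power is about 1.15.

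The point is firmest for Onboarding, which has a restrictive trigger and at most one outcome per person. It is weakest for Short disengaged, whose 24-hour rule can recur. For the MRTs a general shortfall is not shown. It remains for Onboarding unless nearly everyone triggers it.

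The trigger shares, repeat counts, within-person correlation and delivery probabilities used here are assumptions. The reproduction of the pilot figure and the restriction to participants who trigger come from the article, with a two-sided test assumed.

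**What to change.** Keep all enrolment numbers.

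- **Pilot power statement:** replace the blanket 80% with the detectable effect per JITAI as a function of the number of participants who trigger it, as in Step 2. Say that the 80% at d=0.8 applies only to a JITAI that nearly everyone triggers.
- **Pilot reporting:** present the between-arm comparisons as estimates with confidence intervals, giving the number of participants and triggers in each arm.
- **MRTs:** when sizes are finalised after the pilot, state power per JITAI from expected eligible decision points per person, delivery probability and within-person correlation, and say which earlier controls are pooled.

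The cost is a recalculation and revised wording. The downside is that the stated power becomes less favourable for rarely triggered JITAIs.
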